## Study interventions

Communities selected for the intervention arm will benefit from a new cadre of health workers, which will be recruited and trained for the sole purpose of monitoring and supporting all aspects of child development under the age of 2. The newly trained health workers will bear the title of “child development agents” (CDA) and will be community-based. A total of five CDAs will be trained and employed for the project period; their sole responsibility will be to support targeted children and their caregivers with the interventions outlined below. We will ask for community recommendations for the selection of CDAs with the requirement that they have some previous experience in health-related activities and ability to read and write in both English and Tonga, the local tribal language. The CDAs will be employed by the project and work full-time. Each CDA will be responsible for approximately 50 intervention children across three health zones. **CDAs will visit all intervention children on a bi-weekly basis**. In total, CDAs are expected to conduct 100 household visits per month (50 children times two visits each); this will mean that they will each do about five visits per day. **The home visits will have two fundamental functions:**

1. **Ensuring treatment of malnutrition and acute infections**. CDAs will monitor children’s growth using mid-upper arm circumference (MUAC) measurements, if they identify children that have moderate acute malnutrition (defined as absence of edema and MUAC <12.5 and ≥11.5 cm), they will provide supplemental information to the caregiver on how to improve the child’s diet. If the CDAs identify children with severe acute malnutrition (defined MUAC <11.5 cm without edema or MUAC of <11.0 – 12.5 cm with pedal edema), they will be advised to immediately refer the child to the nearest health facility for further evaluation and management. Similarly, CDAs will inquire about symptoms of malaria, acute diarrhea or pneumonia, and instruct parents to seek treatment at the nearest health facility as needed.

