**Intervention in comparison group:**

In the comparison group communities, we will refer any children that during the surveys are identified with fever, cough/difficulty breathing, diarrhea, or SAM/MAM to the nearest health center for evaluation. Otherwise the comparison clusters will continue with the current Ministry of Community Development, Mother and Child Health standard of care. No CDAs will be assigned in the control health zones, and no mothers groups will be organized in the control communities.

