### Routine visits in intervention clusters

Upon completion of enrollment and the baseline survey, enrolled mothers in areas selected for the intervention will be visited by the CDAs. Routine visits will focus on:

1. *Health and Nutrition Monitoring*

Each visit in intervention clusters will start with a review of the child’s health status and an update since the previous visit. CDAs will have previously reviewed the child’s under-5 card and will have reminders on which children are behind with their vaccinations and check-ups. At each visit, the CDA will review the child health card with the caregiver, and inform and refer to the clinic if the child has missed an immunization, health check-up or a routine treatment such as deworming or vitamin A supplementation. The CDA will also remind the mother of upcoming routine health check-ups for the child. The CDA will measure the child’s MUAC[[41](#_ENREF_41)] every month and communicate the result to the mother. If the result shows signs of moderate to severe acute malnutrition or a poor growth pattern, the CDA will refer the child to the clinic. Following WHO/UNICEF guidelines [[42](#_ENREF_42)], we will classify all children as severely malnourished if their MUAC is less than 115 millimeters (11.5 centimeters). In case of malnutrition, the CDA may also work with the mother to suggest an affordable, local, and nutritionally appropriate diet for the child following Ministry guidelines and the ones of the Zambia National Food and Nutrition Commission. The CDA will also ask about presence of acute infectious diseases such as fever, diarrhea, cough or difficulty breathing, worms and refer to the clinic and to a community-based health worker such as a CHA or CHW if any of these are present. The routine visits for health and nutrition monitoring will last for 12 months.

1. *Cognitive Stimulation/Parenting Intervention facilitation and check-up.*

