## Data capture/paper storage

Identifying information including the woman's full name, location of her home and cell phone number (if applicable) will be kept in a study log book that will be carried by each of the CDA and will be kept separately from the medical information about the study participants. All study forms will only contain study identification numbers and will not contain any identifying information. Field monitors will use standardized forms for all data capture at baseline, midline and endline.

At enrollment, a unique study ID will be given to the caregiver and all forms will use this ID to link the forms together. The study ID will have 5 digits. The first two digits will indicate the cluster (health facility) and the final three digits will be the caregiver’s unique identifier. This will be a continuous number, advancing by 1 for each mother enrolled: i.e. 01001, 01002, 01003, 02001, 02002, 02003, etc.

Data collected at enrollment will include contact information for the mother (address/cell phone). As each mother is enrolled, a timeline will be developed for that mother-infant pair. The timeline will be sent to the CDA and reminders near/around the day of the visit will be given to the CDA to follow-up with the mother.

Data collected at baseline and endline will include information on maternal and child health, weight, height, mid-upper arm circumference (MUAC), as well as neurocognitive assessment (endline only) with standardize questionnaires. At the end of baseline and endline assessment, the data collectors will meet with the field supervisors daily to hand in their paper forms.

For the monthly monitoring, data on children in the intervention arm, including MUAC and presence of danger signs of illness, will be collected. The CDA will meet with a data supervisor every two weeks to hand in all monitoring data on the child.

Field supervisors will review the forms for errors/missing data and will ask the CDA or data collector to fix the errors if possible. Hard copies of the data forms will be taken to the main office (Choma), scanned into a PDF and data captured through the TeleForms program.

All paper files will be stored in the central office in Choma in file drawers, ordered by study ID number. The files will be locked and the field director will have keys to those cabinets. At the end of the study, the paper files or electronic images will be stored up to 5 years past the end of the study.

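### A child with pedal oedema and a mid-upper arm circumference above 12.5 cm has no malnutrition class and no explicit referral rule in the protocol

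*Protocol*

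**What the plan says.** Study interventions describes what the child development agent (CDA) does at the home visits. Moderate acute malnutrition is "defined as absence of edema and MUAC <12.5 and ≥11.5 cm"; for these children the stated action is that "they will provide supplemental information to the caregiver on how to improve" the diet. Severe acute malnutrition has two branches: MUAC below 11.5 cm without oedema, or "MUAC of <11.0 – 12.5 cm with pedal edema". Severe cases are referred at once.

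Routine visits in intervention clusters sets out the procedure for the same visits: "If the result shows signs of moderate to severe acute malnutrition or a poor growth pattern, the CDA will refer the child to the clinic". On severity, "we will classify all children as severely malnourished if their MUAC is less than 115 millimeters". Diet advice is an optional extra: "In case of malnutrition, the CDA may also work with the mother to suggest an affordable, local, and nutritionally appropriate diet". Oedema is not mentioned in that section.

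In the comparison arm, children found at surveys with certain acute symptoms are referred, as are those with "SAM/MAM to the nearest health center for evaluation".

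**The concern.** These are referral thresholds for young children, applied by community workers who, under Risks for participants, do not give medical care themselves. Identifying a child who needs the clinic is one of their main functions, so the written thresholds should cover every child they may meet.

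Study interventions treats oedema as a sign of greater severity, since its presence rules out the moderate class. Yet the oedema branch of the severe class stops at 12.5 cm. A child with oedema and a larger arm circumference falls outside both classes. What is at stake is a missed or delayed referral of such a child.

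**Working it through.** No sample size, power or error rate is involved, so the check is one of logic.

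**Inputs**
- Moderate class (Study interventions): no oedema, and 11.5 ≤ MUAC < 12.5 cm.
- Severe class without oedema (Study interventions): MUAC < 11.5 cm.
- Severe class with oedema (Study interventions): a 'less than' sign joined to the range 11.0 to 12.5 cm.
- Severe class, all children (Routine visits): MUAC < 11.5 cm.
- Referral (Routine visits): moderate to severe on the MUAC result, which by MUAC alone means below 12.5 cm.

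**Method.** Take a child with oedema. The moderate class is then impossible. Five readings of the oedema range were run over MUAC 9.0 to 16.0 cm in 0.1 cm steps, first with Study interventions alone and then with the visit procedure's 11.5 cm severity rule. The last column applies the visit procedure's referral sentence, which removes everything below 12.5 cm.

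| Reading of the oedema range | No class, Study interventions alone | No class, with the < 11.5 cm rule | No referral, with MUAC-based referral |
|---|---|---|---|
| 11.0 to 12.5 inclusive | below 11.0; above 12.5 | above 12.5 | above 12.5 |
| 11.0 to < 12.5 | below 11.0; 12.5 and above | 12.5 and above | 12.5 and above |
| anything ≤ 12.5 | above 12.5 | above 12.5 | above 12.5 |
| anything < 12.5 | 12.5 and above | 12.5 and above | 12.5 and above |
| < 11.0 only | 11.0 and above | 11.5 and above | 12.5 and above |

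**Result.** Everything above 12.5 cm (12.6 to 16.0 cm on the grid) is uncovered in all five readings and in every column. Exactly 12.5 cm is uncovered in three of the five. Below 12.5 cm every child with oedema is referred, whichever reading is taken. The lower-end gaps in the second and third columns are therefore missing labels, not missed referrals. At most they cost the word 'immediately', which Study interventions uses and the visit procedure does not repeat.

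**Search for the rule elsewhere**
- Routine visits: the illnesses asked about are fever, diarrhoea, cough or breathing difficulty, and worms. The further trigger of a poor growth pattern does not name oedema.
- Recruitment and baseline survey: weight, height and MUAC are taken, and danger signs reported by the caregiver lead to referral. Oedema is not named.
- Intervention in comparison group: the severe and moderate classes used there are defined with respect to oedema only in Study interventions, so the gap carries over to the comparison-arm surveys.

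No section supplies the missing rule.

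**The case against.** The best case against has four parts.

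*The text may be damaged.* The document was machine-read, so the 'less than' sign may not be the authors' own. No weight should rest on that sign or on the lower bound. The 12.5 cm ceiling remains in the text as shown, and the gap depends only on that.

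*There are backstops.* CDAs can phone a supervisor about referral (Study interventions), are trained in danger signs and anthropometry (Study Procedures), and may refer when they judge it necessary (Risks for participants, which also says that procedures follow ministry guidelines). Each visit opens with a review of the child's health. All of this stands and lowers the risk. A reader might infer that such a child would go without care, and the documents do not support that. They show only that the rule is not written down.

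*The moderate-case difference is not a contradiction.* A reader might infer that moderately malnourished children in the intervention arm go unreferred while comparison children are referred. That would follow only if Study interventions were used alone. It does not forbid referral, the visit procedure requires it, and the two can be followed together. What remains is an inconsistency between an overview and a procedure.

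*Silence in the data list proves little.* The monthly monitoring text says that "data on children in the intervention arm, including MUAC and presence of danger signs of illness, will be collected". A reader might infer that oedema goes unrecorded, but the list is introduced as a partial one, so the omission does not show this.

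**Conclusion.** The referral rule is wrong as written, on a minor scale. Pedal oedema with MUAC above 12.5 cm has no class and no explicit referral action anywhere in the protocol, and this does not depend on how the range is read.

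The finding is limited to that upper end. That every child with oedema below 12.5 cm is referred assumes that the visit procedure's referral sentence is applied to the MUAC value itself, whether or not oedema is present. The assumption is needed only for the '< 11.0 only' reading between 11.5 and 12.5 cm; under the other four readings those children are already severe.

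The number of children concerned cannot be estimated from the document. A reader might go on to infer a bias in stunting or development scores. Nothing in the protocol allows such an effect to be sized, and none is claimed.

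**What to change.** In Study interventions, replace the oedema range with a rule that any child with pedal oedema is referred immediately, whatever the MUAC. The responsible clinicians should confirm the class label. Repeat the rule in Routine visits in intervention clusters, and apply it at the surveys in both arms.

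As a secondary harmonisation, state in Study interventions that moderate cases are also referred to the clinic, with diet advice in addition, as the visit procedure already requires.

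The cost is wording in the protocol and the CDA training, and a few more referrals. Design, sample size and analysis are unaffected.

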**Intervention in comparison group:**

In the comparison group communities, we will refer any children that during the surveys are identified with fever, cough/difficulty breathing, diarrhea, or SAM/MAM to the nearest health center for evaluation. Otherwise the comparison clusters will continue with the current Ministry of Community Development, Mother and Child Health standard of care. No CDAs will be assigned in the control health zones, and no mothers groups will be organized in the control communities.

## Eligibility Criteria

Inclusion

- Children aged 6-12 months in the catchment areas of the five selected health facilities in Southern Province will be eligible to participate
- Child’s primary caregiver must be 15 years or older
- Child’s primary caregiver must be a female (because the participants in the women’s group may feel uncomfortable discussing certain issues if a man is present)
- Health workers working at the five health centers where the study is taking place
- District and provincial level nutritionists or clinical care specialists

Exclusion

- Caregivers who are unwilling to provide informed consent
- Families that plan to move from their health center catchment zone during the twelve month period of the study
- Health workers, nutritionists, or clinical care specialists who refuse to provide informed consent

## Study Procedures

Training of CDAs

Prior to the initiation of the study, the CDAs will participate in a one-week training workshop, which will consist of a mix of didactic and practical sessions. This will include an overview of the study design, description of the study interventions, research ethics and protection of human participants, screening for signs of common infectious diseases and danger signs, and extensive training on the use of the anthropometric toolkits, as well as the comparison of anthropometric measurements with the age-specific reference tables.

CDAs will also receive special training on community-based early cognitive stimulation. The early childhood development training will be based on the UNICEF/WHO curriculum and on the Save the Children Essential Package training. This is the same training that UNICEF and Save the Children have adopted in Zambia after obtaining local ethical clearance and Ministry permission. The workshop will include a careful review of the process of informed consent, importance of confidentiality, and detailed review of the baseline and routine data collection instruments. We will also conduct a post-training test to assess the understanding of study procedures and competence of the CDAs in conducting interviews and performing anthropometric measurements.

Pre-testing data collection instruments

The baseline survey and biweekly data collection forms will be pre-tested with 10 households (caregivers) to assess the clarity of the questions and ensure that appropriate responses are available on the form. After pre-testing the forms will be finalized before the initiation of data collection.

###

### Recruitment and baseline survey

Study staff will visit all villages within the catchment area (both intervention and control zones) of the selected health facilities at the beginning of the study. The study will be introduced to local health authorities, traditional leaders, community leaders, and health center committees. After making sure that the study’ goals and procedures are acceptable to the traditional leaders, community leaders, and health center committees, the CDA will identify potentially eligible children aged 6-12 months through the health center under 5 registries and the village headman’s log book. The CDA will work with the local traditional leaders to locate the families of potentially eligible children. The primary caregiver of the child (hereafter referred to as the caregiver) will be approached, the screening questions will be asked and, if the child is eligible, the caregiver will be asked to provide consent (or assent if the parent is under 18 years old with consent to be provided by the husband if the mother is a minor). Once informed consent has been obtained, the CDA will schedule a time to conduct the baseline survey.

The CDAs will conduct a baseline survey of both control and intervention households which will include: a) basic demographic and socioeconomic status, b) availability of books, toys and other reading material at home, time spent by caregivers reading to the child, as well as time spent by caregivers playing with the child, c) anthropometric screening (weight, height, and MUAC), d) review of vaccinations and child health visits using child health card, e) assessment of maternal or caregiver mental well-being, f) assessment of maternal depression with the SRQ-20 questionnaire, and g) presence of other early childhood development programs in the community. If caregivers report any danger sign during the baseline survey, they will recommend immediate referral to the health facility. If any signs of uncomplicated illness (suggestive of malaria, pneumonia, or diarrhea) are present, the CDA will liaise with the nearest volunteer community health worker (CHW) or community health assistant (CHA), if available in the catchment of the clinic, and refer the child to this person for evaluation. If there is no CHW or CHA in the health zone, the child will be referred to the health center for evaluation. Caregivers will also be asked if they had previously participated to ZamCAT study, and if they would be willing to have the researchers access their baseline data from ZamCAT. Before obtaining permission to review their ZamCAT baseline data, we will obtain written informed consent to access these data.

Households in control health zone clusters will undergo the baseline and endline surveys including an endline assessment of early childhood development. Routine MOH heath facility and community-based activities will continue but none of the aforementioned study interventions will be implemented in the control areas.

Tracking and monitoring system

At enrollment, a unique ID and visit schedule will be created for each child and their caregiver. Each CDA will keep a log of the children that she visits fortnightly. The log will include the ID of each child, the date when the child was visited, and whether there was any referral. The study coordinator will then visit the CDA every two weeks to conduct monitoring activities, record the number of successful and unsuccessful visits, check that the report matches the biweekly forms, verify completion of the biweekly forms and to conduct random monitoring visits to one of the mothers in the intervention arm to verify that the visits have been conducted as reported. The coordinator will also generate a fortnightly report with statistics for the study team to monitor and countercheck with the data coming from the biweekly visits

Whenever there is need for a referral to the health facility as explained in the section below, the CDA will set up a paper based tracking system. She will complete a referral form and hand it to the mother, who will bring it to the health facility during her referral. The health facility staff will then fill in the remaining part of the referral form with diagnosis, treatment and date of visit. The CDA will then pass by the health facility in the following days and collect the form, to confirm that the mother has visited the health facility with her child. The number of referral forms is then recorded during the coordinator’s fortnightly visits.

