### 3.1.2 Internal validity

Power calculations indicate that the selected number of health zones will be sufficient to detect the expected impact on our primary outcomes. After randomization, the soundness of the randomization as a procedure to control for confounding will be checked by comparing variables obtained through the baseline survey and through community level data. Examples of baseline variables that will be compared are maternal age, education and occupation; child age and gender; birth weight of the child; duration of breastfeeding length; and initial vaccination status. We will also include community level baseline variables such as distance to health center and District Medical Office, road access and presence of community health workers. Although blinding of treatment will not be possible due to the very nature of the intervention, we do not expect Hawthorne effects to be significant in this case due to the length of the program. We also do not foresee important concerns due to differential attrition in the two arms because of the long-standing relationship of ZCAHRD in all of these communities (both the control and intervention) established through the previous ZamCAT study.

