# Time Frame

| Development of intervention materials and BU IRB/Zambian ethics committee approvals | Sept 2013 – April 2014 |
| --- | --- |
| Surveyor and CDA recruitment and training | April 2014 |
| Pre-testing data collection instruments, enrollment and baseline survey | May 2014 |
| Intervention rollout | September 2014 |
| Endline evaluation | October 2015 |
| Data analysis | November 2015 |
| Year 1 report and data dissemination | December 2015 |
| Parenting assessment | April 2016 |
| Mothers group extension | April 2016 |
| Year 2 (follow-up) evaluation | November 2016 |

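### CDAs who will serve only the intervention arm find families and measure the baseline in zones already described by arm, and the protocol never says the random draw waits until enrolment closes

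*Protocol*

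**What the plan says.** The Protocol section Recruitment and baseline survey begins: "Study staff will visit all villages within the catchment area (both intervention and control zones". Arm labels are therefore attached to zones at first contact. It continues that "the CDA will identify potentially eligible children aged 6-12 months through the health center under 5 registries", with the headman's log book as a second source, and that "The CDA will work with the local traditional leaders to locate the families of potentially eligible children". Approach, screening and consent are written in the passive voice, so no role is named for them. Study Procedures does train CDAs in the consent process, which suggests that they carry it out.

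On measurement: "The CDAs will conduct a baseline survey of both control and intervention households". That survey covers weight, height, MUAC, parenting items and the SRQ-20.

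Study interventions says of the CDAs that "their sole responsibility will be to support targeted children and their caregivers with the interventions outlined below", and "Each CDA will be responsible for approximately 50 intervention children across three health zones". The text on the comparison group assigns no CDA to control zones.

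Determination of clusters and randomization describes a random draw of half the zones in each facility, stratified by population size and distance. It does not say when the draw happens relative to enrolment or who sees the result. Section 3.1.2 writes "Although blinding of treatment will not be possible due to the very nature of the intervention" and relies on a baseline comparison to check the randomisation. Section 3.1.1 invites all caregivers with a child of eligible age.

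In the Time Frame, CDAs are recruited and trained in April 2014, enrolment and baseline fall in May 2014, and a later row reads "Intervention rollout | September 2014".

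**The concern.** In a cluster trial, randomising zones protects the comparison only if the children who enter from each zone do not depend on its arm. When recruitment follows a known allocation, the enrolled groups can differ even though the zones were drawn fairly. The risk is greater if the person tracing families has a continuing role in one arm only. A CDA might search harder for hard-to-reach families who will become part of her own caseload. Equally, she might be quicker to accept that a family plans to move.

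The planned safeguards cover this only in part. Baseline nutritional status, one of the adjustment variables in Data analysis, is measured by the same CDAs. No baseline table reveals selection on characteristics that were not recorded. The separate endline team protects outcome measurement, not recruitment.

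**Working it through.** **1. Order of events.** The texts on recruitment and on the baseline both use arm labels. The randomisation text gives no timing. Section 3.1.2 mentions a check after randomisation using baseline data, which is compatible with either order. Routine visits start only once enrolment and baseline are complete. So the order is unstated, and the labels make a prior draw the more natural reading.

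**2. The plan's own sample size.** Inputs from Sample Size Calculations: 0.5 SD, power 0.9, 20 children per zone, ICC 0.1. Two-sided alpha 0.05 is assumed because none is stated.
- Unclustered n per arm = 2 × ((1.960 + 1.282) / 0.5)² = 84.06, rounded up to 85.
- Design effect = 1 + (20 − 1) × 0.1 = 2.9.
- 85 × 2.9 = 246.5, against the stated 250 per arm. The figure reproduces, and the timing of the draw does not enter it.

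**3. Standard error at the stated enrolment.** 500 / 30 = 16.7 children per zone.
- Design effect = 1 + (16.7 − 1) × 0.1 = 2.57.
- SE of the difference = √(2 × 2.57 / 250) = 0.143 SD. With 20 per zone and 300 per arm it is 0.139, nearly the same.

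**4. Type I error under a selection shift b.** The shift is assumed, since the documents give no uptake by arm. Formula: 1 − Φ(1.96 − b/SE) + Φ(−1.96 − b/SE).

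| Assumed shift (SD) | Type I error |
|---|---|
| 0 | 5.0% |
| 0.05 | 6.4% |
| 0.10 | 10.7% |

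**5. How such shifts could arise (also assumed).**
- Share affected times mean difference: 0.10 × 0.5 = 0.05 SD; 0.20 × 0.5 = 0.10 SD.
- One arm misses the lowest 10% on a trait correlated r with the outcome: shift = r × 0.195, so 0.06 SD at r = 0.3 and 0.10 SD at r = 0.5.
- Stunting, using the 36% provincial figure in the Summary. One arm enrols 90% of stunted children and all others: 0.324 / (0.324 + 0.64) = 33.6%, a false gap of 2.4 points. At 80%: 0.288 / (0.288 + 0.64) = 31.0%, a gap of 5.0 points. Equal enrolment gives no gap.

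**6. Can the draw wait?** It needs only zone population and distance. Four months separate the May 2014 baseline from the September rollout. With six zones per facility, each facility has three intervention zones whatever the draw, and five CDAs × 50 children = 250, the whole intervention arm. Staffing numbers therefore do not depend on which zones are drawn. CDAs are hired before the baseline, however, so their selection must not depend on the draw either.

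**The case against.** The strongest reply is that nothing shows the CDAs knew the allocation. The arm labels may only tell the reader that both arms undergo the same procedure. Children come from existing registers, every eligible caregiver is invited, and the same kind of recruiter works in both arms. Balance can also be checked on items that owe little to CDA judgement, such as birth weight, vaccinations on the child health card and community-level data. All of this stands and narrows the point. It does not supply a sentence that fixes the order or conceals the draw.

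Some stronger readings are tempting but unsupported:
- **That CDAs recruited knowing the arm, or took consent themselves.** The first is inferred from labels, the second from training content and passive sentences.
- **That 500 to 750 eligible children for about 500 places gave CDAs a choice.** The range follows from roughly 100 to 150 children at each of five facilities, but section 3.1.1 invites all of them. The protocol allows up to 262 per arm.
- **That the protocol rules out masked assessors.** Section 3.1.2 concerns blinding of treatment. On assessors the protocol is silent, and it already separates them from the CDAs.
- **That bias occurred, or in which direction.** No uptake figures are given.
- **That a later draw is free and still available.** This version already cites first-year results, so May 2014 enrolment is past.

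**Conclusion.** The point holds as a weakness in sequence. The protocol lets people who will work in one arm only find families and measure the baseline in labelled zones, and it does not require the draw to wait. It could have waited without changing sample size, power or the timetable. This is a risk of arm-dependent enrolment, not demonstrated bias, and its direction cannot be told from the documents. The illustrated size, type I error from 5% up to about 11%, rests wholly on assumed shifts of 0 to 0.10 SD, with 250 children per arm, ICC 0.1 and two-sided alpha 0.05. The upper end of that range is one fifth of the 0.5 SD design effect size (0.10 / 0.5).

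**What to change.** **Sequence.** State in section 3.1.2, in Determination of clusters and randomization, and in Recruitment and baseline survey that each facility's draw is made only after enrolment and baseline have closed in all its zones. Choose CDAs at facility level so that hiring does not depend on the draw. Name who screens and who takes consent. The small downside is that CDAs cannot be picked from the selected zones.

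**Where the draw or enrolment has already happened.** Report numbers eligible, approached and enrolled by arm, set against the under-5 registries and headman's logs. State the order of draw and enrolment that was actually followed, and describe any enrolment after the draw as a limitation. This costs a modest reconciliation of existing records.

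**November 2016 assessment.** Have the separate assessors work without the allocation list, and complete anthropometry and the child test before the caregiver interview. This presumes that both arms are assessed, as the impact comparison in Objective 10 requires. It needs an instruction and no extra staff. Some assessors may still infer the arm.
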